#### Local Control (LC)

Defined as the absence of local progression of disease of the target lesions during the study period. Operationally, this is the time from enrollment registration to progression of the treated lesion(s). Subjects without local recurrence will be censored at the earliest date of last follow-up or death. Determination of local recurrence will be based on RECIST criteria 1.1 (see Sect. 11.3 below) and assessed on MRI or CT scan imaging at 12 weeks and any additional imaging/clinical assessments performed during the study.

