## Pretreatment evaluation and subject enrollment

Following the multi-disciplinary consultation including a head and neck surgeon and radiation oncologist, patients who meet the inclusion criteria will be screened and approached for eligibility assessment and potential study enrollment. Written informed consent is obtained for all eligible patients prior to commencing any study related procedures.

All potentially eligible and consenting patients who do not meet the exclusion criteria will have a CT simulation of head and neck region. Based on our experience in the head and neck clinic, less than 10% of patients in this population will be unable to tolerate the CT with head and neck immobilization. Patients who cannot tolerate the simulation procedure with immobilization will be treated off study.

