#### Radiation treatment technique

Volumetric Modified Arc Therapy (VMAT), Intensity Modulated Radiotherapy (IMRT) or Cyberknife robotic radiosurgery are preferred treatment techniques for this study and will be determined by the treating radiation oncologist, in consultation with the medical physicist and radiation therapist.

Cone beam CT will be used for daily image guidance and matched to the primary tumour as well as organs at risk. Radiation treatment is to start within 14 days of the CT/MR simulation.

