### Post treatment assessment and evaluations: (Additional file 1).

The patient will be seen at four assessments following completion of therapy at 6 weeks, and then at 3, 6, 12 months. Follow-up imaging with CT and/or MRI of the head and neck region will be performed 10–12 weeks after the last radiation treatment as per the usual standard of care. Toxicity, quality of life questionnaires, ECOG performance status assessment, will be administered at each follow-up visit and the tumour dimensions from clinical examination and/or any diagnostic imaging will be recorded. Any additional follow-up investigations/imaging will be done at the discretion of the oncology team. Regular follow-up after the 12 month visit will continue as per the usual standard of care. A chart review and data extraction will be performed by the clinical research associate to assess local control and progression free survival 2 years after completion of the treatment.

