### Statistical analysis

Tumour response and control will be reported based on all available clinical/imaging measurements and classified using the RECIST criteria. Adverse events will be summarized using the NCI-CTCAE. The number of patients with grade ≥ 2 toxicity will be reported. Any grade 4–5 toxicity or adverse event on the study will be reported. Baseline demographics, tumour characteristics and reason for no surgical management will be reported with descriptive statistics. The baseline Charlson Comorbidities Index, VES13 and G8 scores will be summarized to assess the study population for vulnerability/frailty. Quality of life and symptom scores will be assessed to identify the severity and duration of changes to these scores during and after SBRT. Exact confidence intervals will be constructed for outcomes of interest and statistical significance will be defined as a two-sided α ≤ 0.05 for all analyses other than the primary outcome. No interpolation will occur for any missing information.

All patients who receive at least one protocol defined treatment will be included in all analyses. Any patient registered to this study who does not receive protocol defined treatment will be described, including reasons for not receiving treatment, but will not be included in further analyses.

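### Local control is timed from registration, but only patients who go on to receive SBRT are analysed, so the wait for treatment counts as near-guaranteed event-free time

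*Protocol article*

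**What the plan says.** All references are to the Protocol article.

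- **Time origin.** Local Control (LC): "this is the time from enrollment registration to progression of the treated lesion(s". Patients without an event are handled as follows: "Subjects without local recurrence will be censored at the earliest date of last follow-up or death".
- **Analysis set.** Statistical analysis: "All patients who receive at least one protocol defined treatment will be included in all analyses". A registered patient "who does not receive protocol defined treatment will be described, including reasons for not receiving treatment, but will not be included in further analyses".
- **Path to treatment.** Pretreatment evaluation and subject enrollment places written consent before any study procedure, and then: "All potentially eligible and consenting patients who do not meet the exclusion criteria will have a CT simulation of head and neck region". The expected loss at that step is that "less than 10% of patients in this population will be unable to tolerate the CT with head and neck immobilization"; these patients are treated off study. Radiation treatment technique adds: "Radiation treatment is to start within 14 days of the CT/MR simulation".
- **Other clocks.** Follow-up visits, the scan at 10 to 12 weeks and the study period for best response run from the end of SBRT. The final chart review is to "assess local control and progression free survival 2 years after completion of the treatment".

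**The concern.** The time origin and the analysis set do not match. The rule for registered but untreated patients shows that registration comes before SBRT and that some registered patients may never reach it. Those patients are left out, while everyone who stays in is credited with the waiting time as time in local control. A patient who deteriorates before the first fraction and is not treated takes any early failure out of the analysis. This is the usual immortal-time structure, and it can only favour SBRT.

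Nothing else in the article offsets it. No progression assessment is planned between registration and the first fraction. The RECIST baseline is tied to the start of SBRT: a scan at most 4 weeks before, or otherwise the simulation scan. In the latter case the clock may start before the measurement against which progression is judged.

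Local control is a named secondary objective. In a single-arm trial there is no concurrent group in which the added time would cancel.

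**Working it through.** **The plan's own figures.** The article states no number for local control. Its only design figures belong to the response rate: a Simon two-stage design with 11 then 38 patients, at least 7 and at least 27 responders, and 60% versus 80%. An exact binomial calculation gives α = 0.0970, β = 1 − 0.9042 = 0.0958 and a stage I stopping probability of 0.4672. These match the stated 0.097, 0.096 and 0.467. None depends on the local control clock.

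**Inputs for the shift.**
- True control from first fraction, used as illustrations: 39% at 6 months (the level of the in-field progression-free survival quoted for the earlier regimen in the Background) and 65% at 12 months (the lower end of the SBRT range quoted there).
- Gap d from registration to first fraction: assumed 7 to 28 days. Only the simulation-to-treatment part, up to 14 days, is documented.
- Constant hazard: an assumption.

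**Upper bound: every progression is found when it happens.** Adding d to every time turns the reading at T from S(T) into S(T − d). With h = −ln S(T)/T, the reading is exp(−h(T − d)), with d in months of 30.4375 days.

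- 39% at 6 months: h = 0.9416/6 = 0.1569 per month. At 28 days, d = 0.920 and the reading is exp(−0.1569 × 5.080) = 0.451.
- 65% at 12 months: h = 0.4308/12 = 0.0359 per month. At 28 days the reading is exp(−0.0359 × 11.080) = 0.672.

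| Gap (days) | True 39% at 6 months reads | True 65% at 12 months reads |
|---|---|---|
| 7 | 40.4% | 65.5% |
| 14 | 41.9% | 66.1% |
| 21 | 43.5% | 66.6% |
| 28 | 45.1% | 67.2% |

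A Kaplan-Meier simulation agrees (38 patients, gap uniform on 7 to 28 days, deaths with a median of 5.7 months censored): 38.8% becomes 42.4% at 6 months, and 65.2% becomes 66.6% at 12 months.

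**Lower bound: progression is found only at scheduled visits.** Treatment takes about two weeks, so the visits at 3, 6 and 12 months after completion fall at about 3.5, 6.5 and 12.5 months from first fraction. A gap of 1 to 4 weeks (0.2 to 0.9 months) puts them at about 3.7 to 4.4, 6.7 to 7.4 and 12.7 to 13.4 months from registration. The 6-week visit and the 10-to-12-week scan come before the 3-month visit. On either clock, the detections that fall before 6 months are the same, and so are those before 12 months. Simulated with this schedule, the shift is 0.0 points at both times.

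**In between.** If half of all progressions are found at once through unscheduled assessment (an assumption), the simulated shift is about 1 to 3 points at 6 months and about 1 point or less at 12 months.

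**Times and medians.** These lengthen by the gap in every scenario. At h = 0.1569 the median from first fraction is 0.6931/0.1569 = 4.4 months; from registration it reads 4.6 to 5.3 months.

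**The case against.** The strongest reply is that the effect is small and may be nil where it would most often be read. Visits are sparse and anchored to the end of treatment, so landmark estimates at 6 and 12 months hardly move unless progression is found between visits. That stands, and it sets the lower end of the range. It does not protect the median or the individual times.

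The gap is also assumed. The article does not say when registration happens. Because patients who fail simulation are treated off study, registration after simulation is a possible reading, and the gap would then be at most 14 days. That stands too, and is why the range starts at 1 week.

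The guarantee is not absolute: growth between an earlier diagnostic scan and the simulation scan could in principle be called progression in a patient who is still treated. No such assessment is planned, so this changes little.

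A reader might infer that local control is meant to be tested against the 39% and that SBRT would gain an unfair advantage in that test. The article does not support this. It names no landmark times for local control and plans no comparison with a historical local control rate. It uses the 39% as background to the response-rate hypotheses. That figure is in-field progression-free survival, whereas local control here censors deaths, so the two may not be comparable under any origin. A reader might also infer the same error for locoregional control and progression-free survival, but the article gives no time origin for either. Finally, clocks that differ between visits and a time-to-event outcome are not in themselves a fault.

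**Conclusion.** The mismatch is real and rests on two explicit statements, not on something left to a later document. Its direction is certain: the time-to-event estimate of local control can only be pushed upward. Its size is modest. With an assumed gap of 1 to 4 weeks and a constant hazard:

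- each time to progression, and any median, is longer by the gap;
- a 6-month estimate rises by about 0 to 6 points at a true 39%, depending on how much progression is found outside scheduled visits;
- a 12-month estimate rises by about 0 to 2 points at a true 65%.

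For scale, the binomial standard error of 39% in 38 patients is √(0.39 × 0.61/38) = 0.079, about 8 points, before any loss from censoring. The bias is smaller than that, but it is systematic and avoidable. The crude proportion without local progression, the primary response rate, the sample size and the stopping rule are untouched. This is a minor correction to a secondary outcome.

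**What to change.** In Local Control (LC), start the clock at the date of the first SBRT fraction instead of at registration, so that the origin matches the treated analysis set. State the same origin for locoregional control and progression-free survival; this is for consistency, since none is given now.

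The change is one phrase and needs no new data. The date of the first fraction is already needed for the limit on treatment duration and for the 6-week minimum before a response can be assigned. The cost is a slightly less favourable estimate. Keeping registration as the origin would also be coherent, but only if all registered patients were analysed, which would mean changing the analysis set.

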When conventional surgery and/or radiotherapy are not recommended by the multi-disciplinary team then patients may be treated with shorter, hypo-fractionated radiotherapy with the goal of symptom relief and local control but at the cost of a lower biological dose. Investigators at the Juravinski Cancer Centre published retrospective results from the ‘0–7-21’ regimen using 24 Gy / 3 fractions which was well tolerated and provided temporary symptom relief in 82% of patients but reported 6 month progression free survival of 39% within the irradiated field [7]; a phase 2 study of previously untreated HNSCC patients deemed to have incurable disease used up to 42 Gy/12 fractions and demonstrated similar rates of initial response and symptom relief but a short progression free survival duration of 3.1 months [8]. Stevens et al. reported an institutional experience of palliative radiotherapy in newly diagnosed head and neck cancer patients who were deemed to have incurable disease and received a wide range of dose/fractionation regimens. The median radiation dose was 50 Gy and between 57–82% of patients were reported to have any radiological, clinical or symptomatic response to treatment [9]. In these three studies, the patients were older with median ages of 71, 73, and 77 years- and median survival was short 5.2, 5.7 and 6.2 months [7-9].

With respect to squamous cell carcinoma (SCC) of the skin, there is limited evidence to guide treatment in patients with unresectable or medically inoperable disease, particularly in the head and neck region [10]. There is a need for prospective data on non-surgical treatment options for frail older adults which improve efficacy while limiting the treatment burden [11].

SBRT can limit the number of treatments while delivering a higher, potentially curative dose. An international consortium of 15 high volume cancer centres reported on a survey of practices using SBRT for head and neck cancers [12]. There was heterogeneity in the indications, techniques and doses reported by various institutions. The most common indication was in the setting of recurrent disease and reported doses were in the range of 35–50 Gy in 3–5 fractions. Several institutions reported 1–2 year local control rates of 65–90% with SBRT [12-15] and acceptable levels of toxicity. To our knowledge, there are no prospective clinical studies evaluating tumour response, toxicity and quality of life in previously unirradiated patients.

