## Safety monitoring plan

Patients treated with HN SBRT on this study are anticipated to have significant frailty and co-morbidities that preclude surgery, conventional radiotherapy and systemic therapy. Studies involving a similar patient population at JCC and other centres reported median survival between 5–6 months and deem the treatment intent to be palliative [9-11]. Head and Neck cancer patients in Ontario are known to have a high rate of emergency room visits and hospitalizations [3]. Therefore, it is likely and expected that some patients may be admitted to hospital or die during the duration of the study; this may be caused by complications due to the tumour and associated treatments or for reasons unrelated to the cancer diagnosis.

A data safety monitoring committee (DSMC) consisting of at least two radiation oncologists who are not co-investigators in the study will review all grade 4 or 5 (severe) adverse events. Any severe adverse events will be classified as definitely related, possibly related or not related to the study intervention. Toxicity will be reviewed by the DSMC on a q6 monthly basis or more frequently if unexpected toxicity is observed. If grade 5 toxicity is observed in more than 10% of patients, the protocol will be amended to a lower radiation dose (40 Gy) for REB review, or the study may be closed.

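### Local control is censored at death where about half of similar patients died within 5 to 6 months; if reported as a Kaplan-Meier probability, it overstates how many patients fail locally

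*Protocol article*

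**What the plan says.** In the protocol article, Local Control (LC) is first described as the absence of local progression in the target lesions during the study period. It is then made operational as a time to event, counted from registration to progression of the treated lesions. The censoring rule follows: "Subjects without local recurrence will be censored at the earliest date of last follow-up or death". No estimator is named there or under Statistical analysis, and no local control or local failure figure is given for any time point.

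Other sections describe the expected mortality and the horizon:

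- Background, on three palliative radiotherapy cohorts: "median survival was short 5.2, 5.7 and 6.2 months".
- Safety monitoring plan, on similar patients: earlier studies "reported median survival between 5–6 months and deem the treatment intent to be palliative". The same section says that "it is likely and expected that some patients may be admitted to hospital or die during the duration of the study", and allows that the cause may be the tumour, its treatment or something unrelated.
- Post treatment assessment and evaluations: visits "at 6 weeks, and then at 3, 6, 12 months", then a chart review "to assess local control and progression free survival 2 years after completion of the treatment".

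**The concern.** Death without local progression ends the possibility of local failure. Censoring treats the dead patient as still at risk, with the same future failure rate as those still under observation. When few patients die this hardly matters. Here the protocol's own sources put median survival at about half a year, while local control is to be judged at two years.

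Two readings of a death-censored curve are possible, and both are weak here.

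- **As the share of patients who fail locally**, it is too high, and by an amount that depends on the death rate.
- **As a net rate in a hypothetical setting without deaths**, it requires deaths to be independent of local failure. The Safety monitoring plan makes that doubtful, because it expects that some deaths may come from the tumour.

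The Discussion names better locoregional control as part of the promise of SBRT and looks ahead to a randomized trial. A local control figure that moves with mortality is hard to compare between cohorts with different survival. It also does not tell a frail patient the chance of experiencing local failure.

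**Working it through.** **The plan's own figures.** There is none for local control to reproduce. The article's computed figures concern the Simon design for response. They reproduce (alpha 0.097, beta 0.096, probability of early termination 0.467), and local control plays no part in them.

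**Direction, without any model.** At each failure time with d failures among n at risk, the death-censored complement rises by S_KM × d/n, where S_KM counts only local failures. The cumulative incidence rises by S_all × d/n, where S_all counts local failures and deaths. S_all never exceeds S_KM, so the censored complement is at least as large as the cumulative incidence in any data set, and larger once a death precedes a failure.

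**Inputs for the size**

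- Median survival m = 5.7 months (Background, middle of the three cohorts), with 5.2 and 6.2 as the range.
- Death-censored local control of 75% (assumption), inside the 65–90% at 1–2 years that the Background cites. That range does not fix the time point, so 75% is read first as a 12-month and then as a 24-month rate.
- Independent exponential times to local failure (hazard λ) and death (hazard μ) (assumption). The short interval between registration and the end of treatment is ignored.

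**Formulas**

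- μ = ln 2 / m = 0.6931 / 5.7 = 0.1216 per month
- Local failure with deaths censored: 1 − exp(−λt)
- Cumulative incidence: λ/(λ+μ) × [1 − exp(−(λ+μ)t)]

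**75% read as the 12-month rate**

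- λ = −ln(0.75)/12 = 0.0240
- Censored, 12 months: 1 − 0.75 = 25.0%
- Cumulative incidence, 12 months: 0.0240/0.1456 × (1 − 0.174) = 0.1647 × 0.826 = 13.6%

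**75% read as the 24-month rate**

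- λ = −ln(0.75)/24 = 0.0120
- Censored, 24 months: 25.0%
- Cumulative incidence, 24 months: 0.0120/0.1336 × (1 − 0.0405) = 0.0897 × 0.9595 = 8.6%

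**Sensitivity (same formulas)**

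| Death-censored local failure at time t | Cumulative incidence, t = 12 months, median survival 5.2 to 6.2 | Cumulative incidence, t = 24 months, median survival 5.2 to 6.2 |
|---|---|---|
| 35% (control 65%) | 18.4–20.2% | 11.6–13.2% |
| 25% (control 75%) | 12.9–14.2% | 8.0–9.2% |
| 10% (control 90%) | 5.1–5.6% | 3.1–3.5% |

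If median survival were 12 months (μ = 0.0578), the 75% case would give 25% against 18.3% at 12 months. With 75% as the 24-month rate it would give 25% against 14.0% at 24 months: 0.0120/0.0697 × (1 − 0.1875).

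A simulation with 38 patients agrees with the formulas. With a 6-month median and 65% control at 12 months, mean local failure at 12 months was 35.1% censored against 19.9% as cumulative incidence.

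**How many patients carry the late estimate.** At a 5.7-month median, 38 × 2^(−12/5.7) = 8.8 would be alive at 12 months and 38 × 2^(−24/5.7) = 2.1 at 24 months.

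**The case against.** Censoring at death is not wrong in itself. It is the correct handling for a cause-specific hazard, it is the convention behind many published local control rates, and it tries to isolate what the treatment does to the tumour. The article names no estimator. The opening phrase of the definition and the promise of exact confidence intervals would also fit a simple proportion, which censoring does not inflate. Progression-free survival is a separate outcome, so local control is not the only time-to-event measure. All of this stands, and it is why the point is conditional. It does not remove the point: the article itself fixes a time to event and a censoring rule, so an analysis plan that treated death as competing would contradict it.

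Survival in this trial may also exceed 5 to 6 months. Those figures come from other, palliative cohorts. This trial admits stage T2 disease, skin primaries and patients who declined surgery, and excludes those with a life expectancy of 3 months or less. That affects the size but not the direction.

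A reader might infer more than the documents support:

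- **That inflated 12- and 24-month figures are already in the plan.** None is printed. Those times come from the visit schedule and the chart review.
- **That the 24-month contrast is 44% against 16%.** This follows from carrying a 75% rate at 12 months forward at a constant hazard. It implies 0.75² = 56% local control at 24 months, outside the 65–90% that the Background cites.
- **That the rule flatters SBRT.** It does the reverse, by overstating local failure.
- **That locoregional control has the same fault.** The article gives no censoring rule for it.

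**Conclusion.** The point holds in conditional form. The stated rule, followed as written and summarised as a probability, overstates the share of patients with local failure. On the protocol's own survival figures the censored value is about 1.8 times the cumulative incidence at 12 months (25% against 13.6%). It is about 2.9 times at 24 months if 75% is the 24-month rate (25% against 8.6%). The direction is certain. The sizes rest on independent exponential times, an assumed 75% control rate and survival borrowed from other cohorts, and they shrink if patients live longer.

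The consequence is limited. Local control is a secondary outcome, no test or stopping rule uses it, and the go/no-go decision depends only on response counts. The wording should be changed, but the design does not need to be.

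**What to change.** Under Local Control (LC), replace censoring at death with wording such as: death without local progression is a competing event; patients alive without local progression are censored at last follow-up; local failure is reported as cumulative incidence (Aalen-Johansen) with 95% confidence intervals and numbers at risk at the assessment times, including 2 years. Keep the death-censored estimate as a supportive figure, labelled cause-specific, for comparison with published rates. If locoregional control is analysed as a time to event with the same censoring, handle it in the same way.

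The cost is one change of wording and standard software. Dates of progression and death are already needed for the existing outcomes. The drawback is that the headline figure becomes less directly comparable with published death-censored local control rates, and the supportive figure is there for that comparison.
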